## **“Physical and mental pleasure”**

# **Effects of a Mutual Recovery Intervention on Mental Health in Depressed Elderly Community-dwelling Adults: a Pilot Study**

## **Abstract**

**Objective:** To examine the effects of mutual recovery program intervention in older adults with high risk of depression at communities in Shanghai, explore suitable approaches to improve mental health of community elders and provide basis for future policy making.

**Methods/Design:** The study involves a cluster-randomized controlled trial. Recruitment were completed between July 2012 and August 2012. Using a, we randomize 6 communities (N=237) into either the intervention group (3 communities, n=105) or to a wait-list control group (3 communities, n=132). All participants should meet screening criteria of depression, which is defined by The Geriatric Depression Scale (GDS-15). From March 2013 to May 2013, participants in the intervention group will receive a two-month mutual recovery program intervention, including 7 ninety-minutes, weekly sessions, which are based on a standardized self-designed schedule.

**Discussion:** Mutual recovery is a comprehensive and inexpensive approach for mental health intervention and could be a creative and helpful strategy to promote the mental health in older adults with high risk of depression at communities.

**Keywords:** Depression; Well-being; Community Intervention; Mental Health; Elderly; Cluster Randomized Trial

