## **Data analysis**

PASW 18.0 for Windows will be used for data analysis. Pearson Chi-square test will be conducted to compare the two groups on difference of the classified data on 3 assessments. A multivariate ANOVA will be conducted to explore the differences within groups, at each of the 3 testing points, on the measures of sleep, WHO5 and

GDS-15. A series of repeated measures ANOVAs will be conducted to compare the two groups on all the variables tested across the screening, pretesting and post testing assessments. This approach is flexible and it is possible to model the dependence between observations from the same individual. Multilevel models can be applied to normally distributed and non-normally distributed outcomes; we will choose the most appropriate model based on the data.

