## **Discussion**

Mutual recovery is a comprehensive and inexpensive approach for mental health intervention and could be a creative and helpful strategy to promote the mental health in older adults with high risk of depression at communities. Mutual recovery program focused not just only on what to teach participants but also on how to organize and present the information and skills.

The intervention effect may be diluted by participants that are health. Considering the intervention effect, we choose participants that are at high risk of depression. The elderly recruitment for this community-level intervention trial has been successful in identifying a large sample of residents at risk in Shanghai using recruiters drawn from the neighborhoods

During the design of the trial, there are a number of methodological issues that we need to consider. We do not randomize program group and control group by individuals but by communities. Thus, there may be some confounding factors that we cannot control, such as the economy condition, family construction and so on. What's more, blind method cannot be utilized because of the process of community mobilization and publicity. Since we cannot intervene the participants' daily life, participants in the wait-list condition are not hindered in seeking supplementary help while on the wait-list, so there may exist contamination confounding in the control group.

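### The model is left to be chosen from the data without a rule, and the open choice includes analyses that ignore the six randomised communities

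*Protocol*

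**What the plan says.** The Data analysis section of the protocol makes three commitments:

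- for categorical data, "Pearson Chi-square test will be conducted to compare the two groups on difference of the classified data on 3 assessments";
- for change over time inside each arm, "A multivariate ANOVA will be conducted to explore the differences within groups";
- for the comparison of arms over the three surveys, "A series of repeated measures ANOVAs will be conducted to compare the two groups on all the variables tested".

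It then calls its approach flexible and adds that "it is possible to model the dependence between observations from the same individual". The last sentence reads "Multilevel models can be applied to normally distributed and non-normally distributed outcomes", followed after a semicolon by "we will choose the most appropriate model based on the data".

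On the design, the Abstract gives six communities, three per arm, with 105 and 132 participants. The Discussion confirms that communities, not individuals, are randomised. It treats this as a source of confounding, not as a source of correlated outcomes. On masking, the Discussion says "blind method cannot be utilized because of the process of community mobilization and publicity".

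**The concern.** Three things are left open in one short paragraph.

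1. The rule for choosing the model is the data, with no criterion, no default and no statement that the choice precedes a comparison of the arms.
2. The text passes from repeated measures ANOVA to multilevel models without saying whether the second replaces the first or supplements it.
3. The only dependence named is between observations on one person. Even the multilevel option, as described, need not contain a community term.

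With three communities per arm this matters. An analysis that counts 237 independent people and one that counts six randomised units use very different standard errors and degrees of freedom. If the protocol does not say which one carries the conclusion, an analyst can follow it to the letter and still report a person-level result.

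**Working it through.** The protocol states no alpha, effect size, SD or ICC, so there is no planned figure to reproduce. The arm sizes agree with the total: 105 + 132 = 237.

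**Inputs.** From the Abstract: 3 versus 3 communities, 105 versus 132 people. Assumed: two-sided 0.05, an outcome scaled to SD 1, a difference of 0.35 SD, ICC from 0 to 0.10, equal community sizes within an arm.

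**Step 1, person-level test.** SE = sqrt(1/105 + 1/132) = sqrt(0.01710) = 0.131. Then z = 0.35/0.131 = 2.68, p = 0.007.

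**Step 2, test that respects the community.** SE = sqrt(ICC × 2/3 + (1 − ICC) × 0.01710), where 2/3 = 1/3 + 1/3 for three communities per arm. The reference distribution is t on 6 − 2 = 4 df.

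| ICC | SE | t | p (4 df) |
|---|---|---|---|
| 0 | 0.131 | 2.68 | 0.055 |
| 0.01 | 0.154 | 2.28 | 0.085 |
| 0.02 | 0.173 | 2.02 | 0.11 |
| 0.05 | 0.223 | 1.57 | 0.19 |
| 0.10 | 0.286 | 1.22 | 0.29 |

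At ICC 0 the SE is unchanged, so the move from 0.007 to 0.055 comes from the degrees of freedom alone.

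**Step 3, dependence on the assumed difference.** At ICC 0.02, a difference of 0.25 SD gives p = 0.056 (person level) and 0.22 (4 df), so both are non-significant. A difference of 0.5 SD gives 0.0001 and 0.045, so both are significant. The two analyses disagree over a middle range of differences, not everywhere.

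**Step 4, false-positive rate.** A simulation under no effect used 3,000 runs per setting, communities of 35 (three) and 44 (three), a pre-post correlation of 0.5, and ICC as the community share of residual variance. The repeated measures ANOVA was represented by its equivalent for two time points, a t-test on change. The cluster test was a t-test on six community means. Results for a normal outcome:

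| ICC | ANOVA ignoring community | Cluster test fixed in advance | Either one significant | Added by free choice |
|---|---|---|---|---|
| 0 | 0.053 | 0.054 | 0.082 | 0.029 |
| 0.01 | 0.089 | 0.055 | 0.111 | 0.022 |
| 0.02 | 0.117 | 0.042 | 0.128 | 0.011 |
| 0.05 | 0.196 | 0.048 | 0.201 | 0.005 |
| 0.10 | 0.314 | 0.042 | 0.316 | 0.002 |

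The last column is the fourth minus the second. A skewed outcome gave a similar picture up to ICC 0.05. There, free choice added 0.132 − 0.113 = 0.019 at ICC 0.02 and 0.206 − 0.197 = 0.009 at ICC 0.05.

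**The case against.** The strongest reply is that the sentence is harmless when read whole. Its first half concerns normal and non-normal outcomes, so the choice it describes is most naturally one of distributional form within multilevel models. That is an ordinary question for a score built from 15 yes/no items and for a yes/no insomnia classification. This stands as the likeliest meaning. It does not close the point, because the text does not confine the choice to distribution, sets no rule for it and never names community as a level.

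A reader might infer that the chi-square test, the MANOVA, the ANOVAs and the multilevel models are rival candidates from which the most favourable result is picked. The protocol does not support that. The first three are each stated as analyses that will be done, for different purposes.

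A reader might also infer that the trial rules out masking of everyone, so that the analysis could be steered by an unmasked analyst. The Discussion does not say so. Its reason for not blinding is publicity in the communities, and it is silent on the analyst. Nothing in the protocol shows that any tuning took place.

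It is also fair to say that the 4-df test in the comparison is not named in the plan, that 0.35 SD is a chosen value, and that the simulation attributes most of the inflation to ignored clustering. All three are correct, and the conclusion is sized accordingly.

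Finally, a statistical analysis plan that is not at hand may settle the model. It could do so only by overriding what the protocol states. The objection is to that statement, not to missing detail.

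**Conclusion.** The point holds in a limited form. As written, the protocol leaves the model to the data without a rule or a time, leaves the relation between ANOVA and multilevel models unclear, and recognises only within-person dependence in a trial that randomises six communities. Analyses that ignore the randomised unit are therefore allowed, and the repeated measures ANOVAs are in fact promised.

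For an assumed 0.35 SD difference, the person-level analysis is clearly significant (p = 0.007). The analysis on 4 df is not, at any assumed ICC from 0 to 0.10 (p = 0.055 to 0.29). The main statistical harm is the neglect of community: simulated type I error is 0.12 at ICC 0.02 and 0.31 at ICC 0.10, against a nominal 0.05. Freedom to choose between models is the smaller part, about 0.03 at ICC 0 and about 0.01 or less from ICC 0.02 upward with a normal outcome. These figures rest on the assumed effect, ICC, correlation and alpha. The defect in the text does not depend on them.

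**What to change.** Replace the last sentence of the Data analysis section with one pre-specified between-group model for one named outcome and time, for example GDS-15 at T3. The model should:

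- adjust for the pre-intervention score, which the T2 survey already collects;
- include a random effect for community;
- use small-sample degrees of freedom (about 4), or be replaced by an equivalent cluster-level analysis of the six community means.

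State that this model carries the conclusion on the effect of the intervention, and that the chi-square tests, MANOVA and ANOVAs are descriptive. Limit any data-based change to the distribution or link. Let a written rule decide it, applied to data pooled over arms before outcomes are compared by arm.

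The change needs wording only: no new data, visits or staff. The price is wider intervals and larger p-values than the person-level analyses would give, because six communities carry limited information.

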## **Discussion**

Mutual recovery is a comprehensive and inexpensive approach for mental health intervention and could be a creative and helpful strategy to promote the mental health in older adults with high risk of depression at communities. Mutual recovery program focused not just only on what to teach participants but also on how to organize and present the information and skills.

The intervention effect may be diluted by participants that are health. Considering the intervention effect, we choose participants that are at high risk of depression. The elderly recruitment for this community-level intervention trial has been successful in identifying a large sample of residents at risk in Shanghai using recruiters drawn from the neighborhoods

During the design of the trial, there are a number of methodological issues that we need to consider. We do not randomize program group and control group by individuals but by communities. Thus, there may be some confounding factors that we cannot control, such as the economy condition, family construction and so on. What's more, blind method cannot be utilized because of the process of community mobilization and publicity. Since we cannot intervene the participants' daily life, participants in the wait-list condition are not hindered in seeking supplementary help while on the wait-list, so there may exist contamination confounding in the control group.

## **Funding**

The study was financially supported by the National Science-technology Program for the 11th five-year plan (<http://program.most.gov.cn/>), project number 2009BAI77B06. The funders had no role in study design, data collection and analysis, decision to publish, or preparation of the manuscript.

